## PROTOCOL SYNOPSIS

**English title:** Awake prone positioning with high flow nasal oxygen in critically ill covid-19 patients.

**Swedish title:** Buklägesbehandling med högflödesgrimma vid covid-19.

**Objectives:** Determine if a protocol for prone positioning with high flow nasal cannula or noninvasive ventilation reduces the rate of intubation in awake spontaneous breathing covid-19 patients or patients with other infectious disease with moderate to severe hypoxemic respiratory failure.

**Design:** Multicenter randomized controlled, parallel group, superiority trial.

**Population and Intervention:** 240 adults, 18 years or older with confirmed or strongly suspected infection with novel corona virus SARS-CoV-2 or other infectious disease, ongoing or planned oxygen treatment with high flow nasal cannula or noninvasive ventilation and moderate to severe respiratory failure as defined by a  $\text{PaO}_2/\text{FiO}_2$  ratio of  $\leq 20$  kPa ( $\approx 150$  mmHg) and/or a  $\text{FiO}_2$  of 0.5 required to reach an  $\text{SpO}_2$  of 94%.

Patients will be randomized 1:1 to a prone positioning protocol with a prone position target of 16 hours/day OR standard care.

**Outcomes:** Primary outcome is the rate of intubation. Secondary outcomes include time in prone position, admission to the ICU, time on mechanical ventilation, need for renal replacement therapy, the WHO ordinal scale for clinical improvement and the 7- and 30-day mortality and complication rate.

## GLOSSARY OF ABBREVIATIONS

ARDS          Acute respiratory distress syndrome

COVID-19    Corona virus disease 2019

EELI          End expiratory lung impedance

EELV          End expiratory lung volume

EIT          Electrical impedance tomography

$\text{FiO}_2$           Fraction of inspired oxygen

HFNC          High flow nasal cannula

GCS          Glasgow Coma Scale

ICU          Intensive care unit

LOS          Length of stay

NIV          Non-invasive ventilation

|                  |                                                |
|------------------|------------------------------------------------|
| PP               | Prone position/-ing                            |
| PaO 2 | Partial pressure of arterial oxygen            |
| RLS              | Reaction Level Scale                           |
| SpO 2 | Peripheral capillary oxyhaemoglobin saturation |
| TIV              | Tidal impedance variation                      |
| VAS              | Visual analogue scale                          |

## 2. INTRODUCTION

The COVID-19 pandemic has been rapidly expanding since the first reported case in Wuhan, China in December 2019, now affecting almost all the world's countries/territories/areas with more than 3.000.000 confirmed cases and more 207.973 deaths as of April 29. COVID-19 can lead to pneumonia with severe acute hypoxemic respiratory failure with the need for high FiO2 and invasive ventilation.

HFNC supplies heated humidified oxygen through the nose and has become a mainstay in the treatment of acute hypoxemic respiratory failure in ICUs, reducing the risk of intubation and mechanical ventilation. HFNC increases airway pressure and lung volume directly related to the flow and inversely related to mouth opening and reduces the work of breathing.

The use of PP in ARDS increases the PaO2/FiO2-ratio and reduces mortality in moderate to severe ARDS. PP in non-intubated spontaneously patients- awake PP- is feasible and transiently improves oxygenation in patients with hypoxemic acute respiratory failure. Further, awake PP may decrease intubation rates in patients with moderate ARDS.

Facing an overwhelming inflow of patients with COVID-19 associated severe respiratory syndrome, ventilator shortage has already become a reality in some centers. Further, invasive mechanical ventilation is associated with a high mortality rate. Therefore, strategies to reduce the risk of intubation and mechanical ventilation are needed.

## **2.1 Aim(s)**

The primary aim of this study is to determine the effect on prone positioning with HFNC or NIV on the intubation rate in critically ill COVID-19 patients or patients with other infectious disease with moderate to severe hypoxemic respiratory failure. The secondary aims include time/day in PP, 7- and 30-day mortality, days on ventilator, in-hospital and ICU LOS, incidence of RRT, the need for vasopressors and/or inotropic drugs, the WHO ordinal scale for clinical improvement, and adverse events during PP. In a subset of 30 patients we aim to study the acute effects on lung volume and function with EIT, PaO2/FiO2 ratios, respiratory rate, hemodynamic parameters and effect on dyspnea.

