### 5.3 Other aspect of care for both arms

All other interventions will follow local guidelines at the present hospital and are not affected by the study protocol. A change of oxygen therapy from HFNC to NIV or vice versa is allowed in both groups at the treating physicians discretion, however the protocol for PP is continued. If patients are transported in-hospital, oxygenation by face mask is allowed and the patient can be transported in a position appropriate for adequate monitoring and safety. The decision to intubate is made at the discretion of the treating intensivist. Patient positioning after intubation is not protocolized.

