### 5.4 Protocol termination

Every participant follows the allocated intervention until protocol termination criteria are met. Termination criteria are fulfilled if:

- the patient recovers and standard nasal prongs or open face mask ("oxymask") with a maximal flow of 5 L/min can be used to manage the hypoxemia for at least 12 hours.
- the patient is intubated.

- death occurs.

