### 7.2 Secondary outcomes

- time in PP/day in awake PP if measured. This will vary at different sites and wards.
- cross-over rate to NIV,
- incidence and days of vasopressor and/or inotropic support,
- incidence and days of renal replacement therapy,
- days on ventilator for patients in need of mechanical support,
- number of patients receiving extracorporeal membrane oxygenation,
- in-hospital and ICU LOS,
- complications.
- the 7- and 30-day mortality.
- WHO ordinal scale (Fig 1) for clinical improvement at baseline, day 7 and 30.

*Fig 1. WHO ordinal scale for clinical improvement*

| Patient State  | Description                                      | Score |
|----------------|--------------------------------------------------|-------|
| Uninfected     | No clinical or virological evidence of infection | 0     |
| Ambulatory     | No limitations of activities                     | 1     |
|                | Limitations of activities                        | 2     |
| Hospitalized   |                                                  |       |
| Mild disease   | No oxygen therapy                                | 3     |
|                | Oxygen by prongs or mask                         | 4     |
| Severe disease | NIV or HFNC                                      | 5     |
|                | Intubation and mechanical ventilation            | 6     |

|      |                                                                              |   |
|------|------------------------------------------------------------------------------|---|
|      | Mechanical ventilation
+additional organ support
(pressors, RRT, ECMO) | 7 |
| Dead | Death                                                                        | 8 |

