## 9. ADVERSE EVENTS

All adverse (unfavorable, negative or harmful) events that are related to or possibly related to PP are to be reported by each participating center by the site investigator to the principal investigator on a case specific reporting form and classified as serious if it:

- Results in death
- Is life-threatening
- Requires admission to a higher level of care
- Requires medical or surgical interventions to prevent a more serious adverse event

All serious adverse events will be reported to the trial steering committee within 24 hours of occurrence.

Possible adverse event may be:

- Pressure wounds
- Aspiration
- Cardiac arrest

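### The safety outcome is worded four different ways, and the protocol does not say whether events from proning after intubation count

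*Protocol*

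**What the plan says.** Four places in the protocol describe the safety outcome.

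- **2.1 Aim(s):** the secondary aims end with "the WHO ordinal scale for clinical improvement, and adverse events during PP".
- **Synopsis:** the secondary outcomes end with "the 7- and 30-day mortality and complication rate".
- **7.2 Secondary outcomes:** the list has "complications" with no definition or window. A separate item, "the 7- and 30-day mortality", ties the two time points to mortality.
- **9 Adverse events:** "events that are related to or possibly related to PP are to be reported", again with no window. Pressure wounds and aspiration are among the examples.

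Three further statements bear on which proning is meant. Among the termination criteria in 5.4 is that "the patient is intubated". Section 5.3 says "Patient positioning after intubation is not protocolized". Section 7.2 does use the word awake for the exposure outcome, "time in PP/day in awake PP if measured", but none of the four safety wordings does.

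**The concern.** A safety comparison needs one rule, applied alike to both arms, for what counts and until when. Two of the four wordings (2.1 and 9) make counting depend on exposure to PP, and that exposure differs between arms by design. The other two do not. A site or analyst following 2.1 would therefore report a different complication rate from one following the synopsis.

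The second gap is the phase of care. Proning on the ventilator can occur in either arm once the allocated intervention has ended. If such events are pooled with those from awake proning, the comparison no longer isolates the studied intervention. At stake is whether the reported complication rate can be interpreted. Onset relative to intubation also has to be captured at the bedside, because no later analysis can recover it.

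**Working it through.** **Step 1: the four wordings applied to the same patients.** The protocol states no figure for the safety outcome, so the first check is textual. The cases are hypothetical, and each wording is taken literally.

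| Case | 2.1 | Synopsis | 7.2 | 9 |
|---|---|---|---|---|
| A. Prone arm, wound from awake PP, first seen after turning back, day 5 | no | yes | yes | yes |
| B. Control patient never prone, aspiration, day 5 | no | yes | yes | no |
| C. Either arm, wound arising while prone on the ventilator, day 12 | unclear | yes, by day 30 | yes | unclear |
| D. Prone arm, PP-related injury first seen on day 35, not prone | no | no | not settled | yes |

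No two columns agree throughout. If the synopsis time points belong to mortality alone, its column becomes that of 7.2, and three different rules remain.

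**Step 2: comparability of a count tied to position.** The prone arm targets 16 of 24 hours (5.1.2, Prone positioning arm), so the window in 2.1 is open for up to 16/24 = 67% of the day. In the control arm it is open for h hours, where h is whatever the physician prescribes, possibly zero. Suppose the hourly event rate did not depend on position at all. The ratio of counted events, prone arm to control, would still be 16/h. It equals one only if h = 16.

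**Step 3: how many patients reach the ventilated phase.** Section 8.1 assumes 88% intubated in controls and a 20% decrease. Read as relative, this gives 0.88 × 0.80 = 0.704. The usual two-sided formula with pooled variance, alpha 0.05 and power 90% is

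n = [1.960 √(2 × 0.792 × 0.208) + 1.282 √(0.88 × 0.12 + 0.704 × 0.296)]² / 0.176² = 110 per arm.

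That is close to the stated 112. The absolute reading (68%) gives 89, so the relative one is used here. With 240/2 = 120 per arm, the numbers intubated are 120 × 0.88 = 105.6 and 120 × 0.704 = 84.5, a gap of 21.1 patients.

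**Step 4: possible offset from pooling.** The protocol gives no rate for proning on the ventilator or for injury, so both are assumptions.

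Offset as a share of an arm = (0.88 − 0.704) × proportion proned × injury risk.

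- Middle case, 50% and 20%: 0.176 × 0.5 × 0.2 = 1.8%, or 10.6 against 8.4 events.
- Low, 30% and 10%: 0.176 × 0.3 × 0.1 = 0.5%.
- High, 70% and 30%: 0.176 × 0.7 × 0.3 = 3.7%.

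**Step 5: effect on the risk ratio.** Assume awake-phase risks of 10% (prone arm) and 3% (control), a ratio of 3.33. Let v be the assumed event risk after intubation per intubated patient. Then

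total risk = 1 − (1 − awake risk)(1 − intubation rate × v).

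| v | Prone, 70.4% intubated | Control, 88% intubated | Ratio | Ratio if 40% intubated in both arms (assumed) |
|---|---|---|---|---|
| 10% | 16.3% | 11.5% | 1.42 | 1.98 |
| 20% | 22.7% | 20.1% | 1.13 | 1.60 |
| 30% | 29.0% | 28.6% | 1.01 | 1.42 |

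With equal intubation rates, most of the absolute difference survives: 6.7, 6.4 and 6.2 percentage points, against 7.0 in the awake phase alone. Near-complete cancellation needs both the planned treatment effect and a high event risk after intubation.

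**The case against.** **There may be two outcomes, not one.** Complications and PP-related adverse events could coexist. But 2.1 lists adverse events and no complications, while the synopsis and 7.2 list complications and no adverse events. The terms fill the same slot, and nothing says they differ.

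**Context points to awake PP.** Section 2.1 opens with proning under high flow nasal cannula or noninvasive ventilation. Section 5.1.2 defines the position within the awake intervention, and that intervention ends at intubation. This is a fair reading of 2.1, and it stands as a possibility. It does not settle the synopsis, 7.2 or 9, none of which excludes later proning.

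**The analysis plan may handle it.** A breakdown by phase is often left there. Conflicting definitions within the protocol are another matter, and onset relative to intubation must be on the event form.

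**Masking is not shown.** A reader might infer that the present wording will hide harm from awake PP, or that it disables the safety criterion in 8.2. The documents support neither inference. The proning and injury rates are assumed, and the imbalance exists only if the treatment reduces intubation. In an open-label trial, counting events by exposure or attribution to PP tends to load them onto the prone arm, which is the opposite direction. The 8.2 criterion concerns severe or unexpected events. Pressure wounds are named in section 9 as a possible event, so the ordinary wound count does not drive that criterion.

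**Ventilated-phase events belong to the total effect.** Section 8.3 specifies intention-to-treat, and complications avoided by avoiding intubation are part of what the intervention does. This stands, and it argues against making events truncated at intubation the main comparison.

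**Conclusion.** The inconsistency is established from the text alone: four wordings that give different counts, two of them conditional on an exposure that differs between arms by design. This should be corrected in the protocol. It affects a secondary safety outcome and changes no stated sample size or power figure.

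Whether events from proning after intubation count is left open. Pooling them could dilute a difference from awake PP. The illustrative offset of 0.5 to 3.7% of an arm rests on the intubation rates in 8.1, with the decrease read as relative, and on proning and injury rates that the protocol does not give. The net size and direction cannot be determined from the document. The stronger conclusion, that harm will be concealed, should not be drawn.

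**What to change.** Use one definition in the synopsis, 2.1, 7.2 and 9: complications from randomisation to day 30, in both arms, whatever the patient's position when the event is recognised. Make this the intention-to-treat safety comparison. Day 30 is already the horizon for mortality and the WHO scale, and a day-7 count can be taken from the same records if wanted. In section 9, relatedness to PP can stay as a recorded attribute, but it should not be the condition for counting an event in the outcome.

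Record each event's onset relative to intubation, and tabulate events before and after intubation by arm as a supporting breakdown. Keep that split out of the main comparison, because intubation is a post-randomisation event that the treatment is meant to change, so time at risk before it would differ between arms.

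The cost is onset fields on the event form, wording changes in four places, and a simple attribution rule for injuries that may have begun before intubation but are found after it.

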## **2.2 Meaning**

This study will determine the effect of awake PP with HFNC or NIV on the rate of intubation in severe hypoxemic respiratory failure due to COVID-19 pneumonia or other infectious diseases. The combination of HFNC/NIV and awake PP may be valuable in situations where ventilator resources are overwhelmed by patients in need of invasive mechanical ventilation support. This study will further contribute to the understanding of physiological mechanisms responsible for improved oxygenation previously observed in PP by examining changes in global and regional lung function in a subset of patients.

## **3. STUDY DESIGN**

### **3.1 Study type**

This is a multicenter open labelled randomized controlled, parallel group, assessor blind superiority trial.

### **3.2 Ethical considerations**

Ethical approval will be sought from the Swedish Ethical Review Authority. Written informed consent will be obtained from all participants in the study. This study will be conducted in compliance with all stipulations of this protocol, the conditions of the ethics committee approval, standards of Good Clinical Practice (as defined by the International Conference on Harmonisation), ethical principles that have their origin in the Declaration of Helsinki and all applicable national and local regulations. This study is not sponsored by any commercial entity.

### **3.2 Study setting**

The intervention will be performed in COVID-19 cohort patient wards of infectious disease departments and intensive care units of major hospitals in Sweden.

### **3.3 Study registration**

The study is registered at ISRCTN (<https://doi.org/10.1186/ISRCTN54917435>).

## **4. PARTICIPANTS AND RECRUITMENT**

### **4.1 Number of participants**

240 male or female adults 18 years or older will be enrolled.

### **4.2 Eligibility criteria**

Patients will be randomized in the study only if they meet all of the inclusion criteria and none of the exclusion criteria.

#### **4.2.1 Inclusion criteria**

Each patient must meet all the inclusion criteria to be enrolled in this study:

- Age 18 year or older
- Admitted to the hospital with confirmed or strongly suspected (e.g. due to history, symptoms, radiology, laboratory tests) COVID-19 infection or other infectious disease.
- Moderate to severe hypoxemic respiratory failure defined as a  $\text{PaO}_2/\text{FiO}_2$  ratio  $\leq 20$  kPa (or 150 if mmHg is used) and/or a  $\text{FiO}_2$  of  $\geq 0.5$  to reach a  $\text{SpO}_2$  of 94%
- Oxygen supplementation (ongoing or planned) with HFNC or NIV.

#### **4.2.2 Exclusion criteria**

- Severe nasal obstruction or contraindication to HFNC or NIV.
- Patient unable to lay prone or in the face forward position (e.g. due to morbid obesity, abdominal wounds etc).
- Immediate need for intubation.
- Severe and/or uncontrolled hemodynamic instability.
- Previous intubation for COVID-19 pneumonia (i.e. step-down patients).
- Pregnancy.
- Known terminal illness with life expectancy less than 1 yr.
- Decision not to intubate.
- Inability to understand instructions and/or to cooperate with instructions necessary to complete the allocated intervention.
- Inability to understand oral or written study information.
- GCS less than 14 or RLS less than 2.

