### **4.3 Recruitment, identification and consent of potential participants**

Potential participants will be identified as they change oxygen therapy from standard nasal cannula or mask to high flow nasal cannula or NIV. When a FiO2 of 0.5 is required to reach a SpO2 of 94% the patients will be approached.

Patients will receive oral, followed by written information and provided an appropriate time for consideration and if needed, consultation with the treating physician, a family member, and/or another person of their choice. Written informed consent will be obtained prior to recruitment into the trial. Due to restrictions in transfer of e.g. paper from single patient rooms, the informed consent procedure may include a proxy in the room transferring the information to and from the patient, or a digital transfer (photo of the informed consent form)

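### On the usual direction of the Reaction Level Scale, the RLS half of the consciousness exclusion bars the fully alert patients the trial is meant to enrol

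*Protocol*

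**What the plan says.** The last exclusion criterion in section 4.2.2 of the protocol reads "GCS less than 14 or RLS less than 2". Section 4.2 states how the criteria operate: "Patients will be randomized in the study only if they meet all of the inclusion criteria and none of the exclusion criteria". Meeting one exclusion is therefore enough to bar a patient. Because the two halves of this criterion are joined by an or, meeting either half is enough.

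The glossary expands the abbreviations to "Glasgow Coma Scale" and "Reaction Level Scale" and says nothing more about either scale. The criterion appears only once, and nothing elsewhere in the protocol restates or corrects the RLS cut-off.

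Three other places describe the patients the trial wants:

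- The synopsis objective asks whether the positioning protocol "reduces the rate of intubation in awake spontaneous breathing covid-19 patients" (it goes on to include other infectious disease).
- Section 4.2.2 also excludes "Inability to understand instructions and/or to cooperate with instructions necessary to complete the allocated intervention", and separately excludes patients who cannot follow the study information.
- Section 4.3 states: "Written informed consent will be obtained prior to recruitment into the trial".

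**The concern.** The two halves read as one consciousness threshold expressed on two scales, so both should exclude the same kind of patient. Both are written as a value below a cut. That works for both only if a low value means reduced consciousness on each scale. If the Reaction Level Scale starts at 1 for a fully alert patient and rises as responsiveness falls, "RLS less than 2" points the wrong way and selects alert patients for exclusion.

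What is at stake is whether the criterion can be applied as written. A screener who scores RLS and follows the text would turn away the patients the trial needs. A screener who follows the evident intent would randomise patients who, on paper, meet an exclusion. Section 3.2 (Ethical considerations) commits the study to comply with everything the protocol stipulates, so those patients would count as formal eligibility violations.

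**Working it through.** The protocol gives no figure to reproduce on this point. The check is to set the criterion against each possible direction of the scale, and then against the rest of the protocol.

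**Inputs from the protocol**

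- Exclusion rule: GCS < 14 or RLS < 2 (section 4.2.2).
- One exclusion is sufficient to bar randomisation (section 4.2).
- Intended patients: awake (synopsis), able to understand and cooperate (section 4.2.2), giving written consent (section 4.3).

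**Inputs assumed, because the protocol does not give them**

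- GCS: a higher score means more alert.
- RLS: whole-number levels from 1 to 8. In the usual direction, 1 is fully alert and 8 is the deepest coma. The reverse direction is also examined.

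**Step 1: which levels the RLS half removes.** Applying RLS < 2 to levels 1 to 8 excludes {1} and keeps {2, 3, 4, 5, 6, 7, 8}. The top of the range does not matter to this step. On any whole-number scale starting at 1, a cut below 2 catches level 1 and nothing else.

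**Step 2: what that means in each direction.**

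| Assumed direction of RLS | Removed by RLS < 2 | Not removed by the RLS half | Compared with GCS < 14 |
|---|---|---|---|
| Usual: 1 = fully alert | Fully alert patients only | Every level of reduced responsiveness | Opposite |
| Reverse: 1 = deepest coma | The deepest level only | All other levels | Same direction; whether the cuts match depends on anchors the protocol does not give |

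**Step 3: the combined clause in the usual direction.** A patient passes only if neither half applies, that is, GCS ≥ 14 and RLS ≥ 2. Where both scales are scored, the clause leaves only patients who are not at the alert level on RLS but still have a GCS of at least 14. A fully alert patient at RLS 1 fails whatever the GCS.

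**Step 4: against the rest of the protocol.** The synopsis wants awake patients, section 4.2.2 wants patients who can understand and cooperate, and section 4.3 wants patients who can consent in writing. A fully alert patient is the plainest example of all three. On the usual direction, that patient meets an exclusion. The passages cannot all be applied as written where RLS is scored.

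**Step 5: what still bars an obtunded patient.** If the RLS half fails to remove someone with reduced consciousness, these other barriers remain: GCS < 14 as its own half of the clause, the exclusion for inability to understand or cooperate with instructions, the exclusion for inability to understand the study information, and written informed consent (sections 3.2 and 4.3). The RLS half does not do its job, but it does not override these.

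**The case against.** The strongest objection is that the point depends on something the protocol does not contain. The glossary only spells out the name of the scale, so the conclusion that alert patients are excluded comes from an assumed direction. This is fair, and the conclusion is stated conditionally for that reason. It does not remove the point. The direction assumed is the ordinary one for a standard scale, and a criterion whose direction the reader must supply is itself in need of repair.

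The second objection is practical. The literal reading clashes so plainly with the rest of the protocol that a screener would notice and apply the intent. This also stands, and it is the main reason the point is minor.

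A reader might infer more than the protocol supports:

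- **That the clause lets unconscious patients into the trial.** An exclusion that fails to catch a patient does not admit that patient. The GCS half, the cooperation and understanding exclusions and the consent requirement all still apply.
- **That centres using different scales enrol different populations.** The protocol does not say that centres choose one scale or that any centre scores only RLS. The cooperation, understanding and consent criteria are the same everywhere.
- **That the two halves are irreconcilable in whichever direction the scale runs.** In the reverse direction the mismatch depends on the number of levels and on how they correspond to GCS. The protocol gives neither.
- **That the inequality was copied across from GCS.** This is plausible, but the protocol does not say how the criterion was drafted.
- **That RLS values exist for enrolled patients and can be audited.** Section 7.2 (Other parameters) lists neither GCS nor RLS among the baseline data, and no screening form is shown.

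**Conclusion.** The point holds as an eligibility-wording error. Assuming the usual direction of the scale, the RLS half excludes fully alert patients, runs opposite to the GCS half, and contradicts the awake, cooperating and consenting population the protocol describes. Followed literally, it makes intended participants ineligible wherever RLS is scored. Followed by intent, it turns those randomised there into formal eligibility violations.

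The point is minor. The practical effect is probably limited, because sites are likely to read the clause by intent and obtunded patients are barred by several other requirements. The number of patients affected cannot be estimated, since the protocol does not say how often RLS is scored; the share of centres could be anywhere from 0% to 100%. The sample size and analysis figures do not depend on this criterion and are unaffected.

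The conclusion rests on one outside assumption, the direction of the Reaction Level Scale with level 1 as fully alert. If the sponsor works with a version that runs the other way, the contradiction with the alert population falls away. What would remain is that the protocol does not give the anchors needed to tell whether the two cuts correspond.

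**What to change.** Amend section 4.2.2 so that the two halves agree and both exclude reduced consciousness. Either of two routes would do:

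- Delete the RLS clause.
- Keep it, with the direction and level restated as the sponsor defines them and the scale's anchors given beside the criterion or in the glossary.

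The choice of route and level is the sponsor's; this review proposes no cut-off. Any screening form in use should be brought into line with the amended text.

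The cost is a one-line amendment and, where a form exists, a matching edit. No change to the sample size or analysis follows.
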